## Abstract

**Background:**

Self-regulated learning (SRL) is described as a process whereby learners actively take control of their learning by setting goals, planning, monitoring, evaluating, and adjusting their learning strategies to improve performance and achieve desired outcomes Panadero (Front Psychol 8:422, 2017). SRL proficiency has been shown to predict educational success and lifelong outcomes, such as income and health. While SRL is recognised as a key lifelong competency, there remain questions regarding how educators can best develop and promote SRL in school settings. A scalable, low-cost intervention targeted at grade 1 students (6–7 years old) in Germany was found to have substantial effects on impulse control and self-regulated learning, with sustained impacts on long-term academic success Schunk (Nat Hum Behav 6(12):1680-90, 2022). This study protocol seeks to adapt the Schunk et al. (2022) randomised trial to the Australian content and extend it to grades levels 2, 4 and 6.

**Methods:**

We will use a standard pragmatic clustered (by school) randomised controlled superiority trial with an additional population-wide matched parallel control arm. Effectively, we will conduct three trials—one for each age/grade level. Each trial will be powered to assess the impact of the intervention on the age/grade groups independently: grade 2 (early primary, 7–8 years), grade 4 (mid primary, 9–10 years), and grade 6 (late primary, 11–12 years). Schools assigned to the treatment group will have all three grade levels (grades 2, 4, and 6) receiving the treatment (at least one class per grade); no classes in the schools assigned to the control group will receive the intervention. A minimum of 56 schools with an average cluster size of 19 children/class will be required to detect a minimum impact of 0.25 SD effect size at 80% power taking into account the clustered design with an intraclass correlation coefficient (ICC) of 0.05. This results in a total sample of 1064 per grade and thus 3192 students in total (56 schools per arm × 19 students in an average-sized class × three grade levels). Randomisation will occur on a 1:1 ratio, such that half of the schools (*n* = 28), and effectively about half of the students (*n* = 1596) will receive the intervention. The primary outcome will be improved self-regulation assessed at 6 weeks, 6 months and 12 months post the intervention. Longer-term secondary outcomes will include academic and wellbeing measures obtained through administrative data linkage to the National Assessment Program in Literacy and Numeracy (NAPLAN) outcomes and the Wellbeing and Engagement Collection (WEC) outcomes measures in the year following implementation (grades 3, 5, and 7). Follow-up via the South Australia Data Linkage Systems will allow for longer-term academic outcomes, mental health, school completion, criminal justice, and tax data.

**Discussion:**

This protocol paper provides a detailed record of the trial design. We also discuss our analytical plan, especially highlighting the opportunities associated with the linkage of the trial participants to South Australia’s population-wide administrative data linkage systems.

**Trial registration:**

ACTRN12623001331628. Registered on 9th of November 2023.

## Introduction

### Background and rationale {6a}

The terms metacognition, self-regulation, and self-regulated learning appear frequently in the educational literature and are often used in closely related contexts. Metacognition is described as the developmental aspects of how one monitors or thinks about one’s own cognition [1] or ‘thinking about thinking’ [2]. Self-regulation (SR) refers to the capacity to regulate attention, emotion, impulses, and behaviour directed at pursuing individually valued goals. The term self-regulated learning (SRL) is the application of metacognition and self-regulation in the context of education and learning settings.

An ever-growing body of research demonstrates that a child's early SRL plays a crucial role in their school readiness, school achievement, and in a range of later life outcomes [3–5]. Alternatively, poor SRL has been linked to low academic motivation, engagement, and achievement [6]. Studies undertaken in English speaking schools suggest that children experiencing risk, particularly those experiencing cumulative risk (e.g. being low-income and having English as a second language), are an important population for support interventions that seek to develop student SRL proficiency [7, 8]. Further, some research has demonstrated that disadvantaged children benefit the most from early SRL interventions [9] and as such, may be seen to be an effective policy investment to enhance equity.

The number of comprehensive intervention studies that target SRL in primary school aged students is growing. However, to date, these remain largely domain-specific, and the transferability of these skills across school subjects is unclear. For example, the association between SRL and academic performance seems to be particularly strong in the case of mathematics (see [10–15]). Similarly, research on the impact of SRL interventions on students’ reading and literacy comprehension also shows positive effects [3, 16]. In the Australian context, Harding [17] examined student SRL in maths and reading in grades 5, 6, 7, and 8 in 42 Victorian schools [17] demonstrating that higher-performing students regulate their learning to a higher proficiency than their lower-performing peers (utilising a self-report assessment of SRL).

A systematic review and meta-analysis published in 2018 highlights that SRL strategies can positively impact primary and secondary school children without requiring a heavy burden on teacher or student time and should be embedded into teaching practices [18]. The review demonstrated that SRL mindfulness-based interventions even of a short duration (6 months or less) had significant and lasting impacts on adolescent SRL [18]. For instance, children participating in a Head Start program in the US benefitted most from a short classroom-based intervention [14]. The authors suggested shorter interventions can have long-lasting impacts and influence student success. Studies noted in the review support the proposition that short-term interventions can be beneficial; however, the research has been largely limited to one age group. It is unclear if similar long-term effects are found across multiple ages and student populations.

In a meta-analysis by Xu et al. [19], the relationship between SRL and academic achievement in K-12 for online and blended educational contexts was examined. Their analysis supported the findings of an earlier meta-analysis by Dignath and Büttner [20], which looked at the effects of SRL interventions on academic performance, strategy use, and student motivation based on 49 primary-level and 35 secondary-level studies. Both analyses indicated that interventions had a higher effect size for primary school students than secondary students in terms of academic performance. For primary students, social cognitive theory-based programmes showed greater effect sizes than motivation or metacognition strategies. However, Dent and Koenka [21] noted that the strongest correlation between metacognitive strategies and academic outcomes was found among early primary students (K to grade 2), which weakened in later primary years (grades 3 to 5). The authors suggested that the weakening of effects may be due to the assessment methods used.

It is clear that whilst there is a growing body of research on SRL, important knowledge gaps remain. For instance, it is unclear if SRL skills transfer from one subject to another, or if they are domain-specific skills. Further, there are very few studies that examine multiple student populations conjointly and employ consistent outcome measures. Randomised control trials are rare, especially with long-term follow-up across a broad socio-economic spectrum. This study protocol presents a trial which aims to build on and somewhat replicate that of Schunk et.al. The Schunk et.al. study represents a scalable intervention that has shown a moderate to high impact on later academic outcomes. Conducted in Germany, the study demonstrated that 5 h of SRL training delivered over 5 weeks significantly impacted grade 1 student’s impulse control and self-regulation behaviour in the classroom. The authors also showed lasting improvements in academic skills including reading and identifying careless mistakes, which were targeted by their SRL intervention.

This trial will determine the impact and acceptability of the SRL intervention including the experiences and practical considerations of participants in the classroom. The training and implementation of the intervention in the school setting will build momentum within the education system and the findings of the trial provide robust evidence for scale-up. The trial will contribute to the academic literature in the following unique ways: it will determine the impact of a short-term scalable SRL intervention on multiple outcomes (self regulated learning skills, literacy, numeracy, self-esteem, resilience, perseverance, emotional regulation, positive relationships with others, student engagement with learning, and attendance) and for multiple grade levels within primary school. Further, the trial is powered to determine if the intervention enhances equity by lifting those students from disadvantaged backgrounds with greater magnitude. Lastly, too few studies are replicated in science, and this trial provides an opportunity to determine if we can reproduce the effects found by Schunk et al. (2022) within an Australian setting.

### Objectives {7}

Adapt the SRL intervention as utilised by Schunk et al. to the Australian context and to different age groups to allow for pragmatic implementation at scale within the South Australian public education system.Investigate the effects of the SRL intervention by different grade levels and by socio-economic position.Provide novel insights into the mechanisms underlying a potentially positive treatment effect.Evaluate results and cost-efficacy of the intervention for potential scale-up within South Australia.

#### Specific hypotheses

We hypothesise the Australian adaption of the SRL intervention will increase primary school children’s self-regulated learning skills as measured by teacher ratings of self-regulated learning 6 weeks, 6 months and 12 months after the intervention, compared to the control group.Our secondary hypotheses are that children who received the SRL intervention will see mid- to long-term improvements inStandardised achievement testing scores as measured by the National Assessment Program in Literacy and Numeracy (NAPLAN),Attendance and behavioural problems based on administrative records, andVarious wellbeing domains as measured by the Wellbeing and Engagement Collection (WEC)when compared to the control group.

For all hypotheses, we will compare heterogeneity in treatment effects by grade level and socio-economic position.

## Methods: participants, interventions and outcomes

### Trial design {8}

Pragmatic clustered by school with one class per grade level, parallel-group, randomised controlled superiority trial. Randomisation occurs at the level of the school to ensure no contamination across school grades (i.e. a school randomised to the intervention group will implement the intervention in grades 2, 4 and 6). Study participants will be consented for their data to be linked to administrative records allowing an additional population-wide matched parallel control arm. Our trial will follow the SPIRIT Guidelines [22] and relevant CONSORT statements [23, 24].

### Study setting {9}

The trial will be implemented across metropolitan, inner regional and rural areas of South Australia. Self-regulated learning is currently not a subject or a specified outcome within the Australian curriculum.

### Eligibility criteria {10}

Schools that have at least 15 students within one class in grade 2, grade 4, and grade 6 will be included. Those South Australian Government Primary Schools who meet these criteria, will be invited to participate by the Department for Education. The intervention will be delivered in grades 2, 4, and 6. All students within the selected classes will participate in the study. There will be no exclusion to the trial at class or individual child level. The invitation to schools will make it clear that it is expected that as part of agreeing to take part in the trial that they will be required to take part in the annual Wellbeing and Engagement Collection (WEC).

### Who will take informed consent? {26a}

School Principals will consent to their schools taking part in the trial. As a pragmatic trial, schools will deliver the intervention in their classes just as they would any other class content. Consent at the student level will not be required. Data collection will be undertaken by the schools with support from the central Department for Education. This data will then be linked to other administrative holdings within the Department before extraction and de-identification. Data will be provided to the academic team in a deidentified format for independent analyses.

### Additional consent provisions for collection and use of participant data and biological specimens {26b}

N/a as no biological specimens are collected.

## Interventions

### Explanation for the choice of comparators {6b}

In the control condition, teachers will continue their teaching practice as normal—i.e. standard practice.

### Intervention description {11a}

The intervention will be based on the Schunk et al. (2022) study. The intervention consists of a set of lessons introducing the process of Mental Contrasting with Implementation Intentions (MCII). MCII is a self-regulation technique that combines two cognitive strategies to help individuals achieve their goals [25]. The first strategy, mental contrasting, involves contrasting a desired future with the present reality to identify any potential obstacles that may hinder progress towards the goal. The second strategy, implementation intentions, involves creating specific plans that outline how and when the individual will take action towards the goal. Together, these two strategies can help individuals develop a clearer understanding of their goals and the steps needed to achieve them. By mentally contrasting the future and identifying obstacles, individuals can prepare for potential challenges and develop effective implementation intentions to overcome them. The MCII approach has been shown to be effective in various domains, including health behaviour change, academic achievement, and goal attainment [3, 26]. The learning lessons are directly tied to the teaching of skills that are fundamentally important for school children including practising reading and monitoring their own mistakes.

### Criteria for discontinuing or modifying allocated interventions {11b}

There will be no criteria for discontinuing or modifying the intervention. Being a pragmatic trial, it is understood that not all students will receive the full “dose” of the intervention should they be absent on the day that a lesson was taught. In all circumstances, dose and implementation fidelity will be recorded.

### Strategies to improve adherence to interventions {11c}

All teachers within the intervention arm will receive standardised training. Scaffolding resources (posters, booklets, videos) will be standardised. Training attendance will be required prior to delivering the intervention.

### Relevant concomitant care permitted or prohibited during the trial {11d}

We are aware of an existing support program provided by the Department for Education aimed at providing professional development to school staff. This program primarily provides generalist information regarding self-regulation within a therapeutic framework, rather than a focus on self-regulated learning. The professional development is provided at the school level by occupational therapists and given staffing levels they operate under a waitlist. Their 2024 waitlist will be matched with our sample prior to randomisation and stratified accordingly.

### Provisions for post-trial care {30}

There will be no provisions for post-trial care.

### Outcomes {12}

#### Primary outcome

The primary outcome will be the student’s Self-Regulated Learning at 6 months post-implementation of the intervention, as assessed by the student’s teacher using a brief rating scale consisting of 14 items.

#### Secondary outcomes

Self-regulated learning will also be measured by the brief teacher-rated scale at 6 weeks and a student self-report measure with the same items will be utilised for grades 4 and 6. The student instrument will be implemented at 6 weeks, 6 months and 12 months post the intervention. Standardised academic achievement tests, Wellbeing and Engagement Collection (WEC) domains [27], school engagement, attendance and behaviour data will be obtained from the Department for Education through administrative data linkage.

#### Longer-term secondary outcomes

Academic and wellbeing measures will be obtained through administrative data linkage by the Department for Education. This will include the National Assessment Program for Literacy and Numeracy (NAPLAN) [28] undertaken for all students in grades 3, 5, 7 and 9 and the Wellbeing and Engagement Collection which is undertaken annually for all students from grade 4 through to grade 12. Data can be linked longitudinally at an individual level.

#### Covariates

Covariates will be obtained through linked education administrative data and will include the geographical socio-economic status of the primary residence of the child, parent's highest level of education, measures of reading abilities (as an indicator of pre-intervention cognition), disability status, school card status (poverty indicator), and prior school attendance records.

#### Exposure variable for per protocol analyses

Primary analyses will be intent-to-treat; however, student attendance for all sessions of the intervention will be obtained from departmental records. As such, we will undertake an additional per-protocol analysis where a student will be defined as receiving the intervention if they attended all sessions.

#### Costing data

Full cost details will be captured including upfront investment costs (e.g. resources, infrastructure, technical support, pre-service training) and recurrent costs (e.g. professional development, administrative support).

### Participant timeline {13}

Socialisation of the trial will be undertaken from November 2023, with school recruitment occurring at the same time. In the third school term, all intervention resources will have been fully adapted to the Australian context and modified to be appropriate for the three different grade levels.

Each of the four school terms is approximately 10 weeks. The teacher training will ideally be implemented late in the first term. The intervention will commence in all treatment schools across the three different grade levels in term 2 2024 (commences 29th April). We will provide video-based tutorials prior to each lesson of the intervention to remind teachers about the specific contents. Ideally, the intervention will be delivered from weeks 3 to 9 in terms 2, with flexibility given due to teacher sickness or other unforeseen disruptions.

Limited trial-specific measurements will be collected pre and post-intervention to ensure as low a burden on the school system as possible. Where possible, all data pertinent to the trial will be collected via administrative data collection. Depending on the assessment these are collected at different times of the year and for different grade levels. Trial participants will be linked to the Department’s administrative data systems with a longitudinal data set linked and generated for analyses. Extractions from the Department systems will occur once per term post-completion of the intervention, with impact determined on the different outcomes as the students age into and thus complete the various outcomes of interest (Fig. 1).

**Fig. 1 Fig1:**
[figure not shown]
Schedule of enrolment, interventions, and assessments*

### Sample size {14}

A sample of (at least) 56 schools will be required with at least one class in grade 2, grade 4 and grade 6, with an average cluster size of 19 children/class to detect a minimum impact of 0.25 SD effect size on the primary outcome with (at least) 80% power while accounting for the clustered design with an intraclass correlation coefficient (ICC) of 0.05. This results in a total sample of (at least) 56 clusters with an estimated 3192 students (or 1064/year level).

### Recruitment {15}

The Chief Executive of the Department for Education will invite schools to participate in the study. The department will facilitate the communication, departmental liaison and engagement with schools. Schools fulfilling the eligibility requirements can actively sign up for the study and will subsequently be randomised into treatment and control groups. Within each primary school a grade 2, 4, and 6 class will be randomly selected from the school class lists. Students in the classes will all receive the intervention in Term 2, 2024. Term 2 was selected as it is a “quieter” term, with the students more settled in class. This time frame also allows for a full 12 months before the primary academic outcomes are collected (NAPLAN). Given the uncontentious nature of the study, parental and student passive/opt-out consent will be employed for the trial.

## Assignment of interventions: allocation

### Sequence generation {16a}

Schools will be the level of randomisation and class the level of implementation. Randomisation will be stratified by socio-economic status blocks (using the Socio-Economic Indexes for Areas (SEIFA) indicator [29]) and metropolitan vs. non-metropolitan areas. The allocation sequence will be generated using computer-generated random numbers in Stata. Specifically, three block randomisation lists, one for each SES stratum will be generated with block sizes of 4 to ensure balanced allocation within each stratum. The advantage of numerous classes within the one school grade level has limited advantage for sample power due to the design effect associated with clustering. As such, at least one class per eligible grade level will be randomly selected for the intervention. Teachers will implement the intervention at the class level. The trial will be powered to assess the impact of the SRL intervention on three grades independently: grade 2 (early primary), grade 4 (mid primary), and grade 6 (late primary). The intervention will be implemented in literacy/reading lessons. Class lists will be provided by each of the participating schools for the process of randomisation. Note that schools in the treatment group may decide to implement the SRL intervention in more than one class within the school; however, only selected classes will be enlisted for the study. Schools in the control group will be required to not use the intervention (not even for non-enlisted classes).

We note that more than the required sample of 56 schools may wish to participate. As such we consider 56 as the minimum sample size, however the resultant study may be larger. Additionally, schools not meeting the eligibility criteria may still wish to participate in the study, for example, rural schools with multigrade classes. For such schools, we will include them as additional samples and block randomise accordingly.

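### The protocol contradicts itself on the stratification factors: SES, metropolitan status and a program waitlist are declared, but the three lists described are indexed by SES alone

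*Protocol article*

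**What the plan says.** Three statements in the protocol article bear on this.

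- **Sequence generation {16a}, declared factors.** "Randomisation will be stratified by socio-economic status blocks", measured by SEIFA, "and metropolitan vs. non-metropolitan areas". That makes two factors.
- **Sequence generation {16a}, mechanism.** The sentence that spells out how this is done provides for "three block randomisation lists, one for each SES stratum will be generated with block sizes of 4", with the stated purpose "to ensure balanced allocation within each stratum". Location does not appear in it.
- **Relevant concomitant care {11d}.** On an existing Department program of staff professional development: "Their 2024 waitlist will be matched with our sample prior to randomisation and stratified accordingly". That makes a third factor, which Sequence generation {16a} does not mention.

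The unit is the school ("Schools will be the level of randomisation and class the level of implementation"). Sample size {14} sets the number: "A sample of (at least) 56 schools will be required". The Abstract gives equal allocation, 28 schools per arm.

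**The concern.** The number of lists and what indexes them determine which factors are balanced by design. The text fixes both, and they do not match the factors it declares. Someone generating the sequence from {16a} alone would balance SES, leave location to chance, and have no reason to know about the waitlist.

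With about 28 schools per arm, school-level balance is not assured by numbers alone. The protocol is also the record of what constrained the allocation. The eventual report and any analysis adjusted for the stratification factors depend on it, and two sections now give different answers. Finally, {11d} relies on stratification to deal with the one piece of concomitant support it identifies, and {16a} provides no means of doing so.

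**Working it through.** **Step 1. Count the lists.** In stratified block randomisation the number of lists is the product of the factor levels. SES has 3 levels (implied by three lists, one per SES stratum), location has 2, and waitlist status has 2 (on or off; this coding is assumed).

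| Factors | Lists | Schools per list at 56 |
|---|---|---|
| SES only | 3 | 56/3 = 18.7 |
| SES × location | 3 × 2 = 6 | 56/6 = 9.3 |
| SES × location × waitlist | 3 × 2 × 2 = 12 | 56/12 = 4.7 |

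The protocol's figure of three is reproduced by SES alone. The two factors declared in {16a} need six. The wording ties each list to one SES stratum, so the three cannot be read as combined SES-and-location strata.

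**Step 2. Size of the imbalance in location.** Allocations were simulated for 56 schools, three equal SES strata and permuted blocks of 4. The gap is the absolute difference between arms in the number of non-metropolitan schools. The documents give no non-metropolitan share, so it was varied.

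| Lists | Assumed non-metro share | Mean gap | Gap ≥ 4 | Gap ≥ 6 |
|---|---|---|---|---|
| 3 (SES) | 25–50%, same in each SES stratum | 2.6–3.0 | 29–36% | 9–15% |
| 3 (SES) | 65/30/10% across SES strata | 2.5 | 27% | 9% |
| 3 (SES) | 80/20/5% across SES strata | 2.2 | 20% | 4% |
| 6 (SES × location) | 25–50%, same in each SES stratum | 1.2 | about 2% | under 0.1% |

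The second and third rows show that SES lists balance location in part when the two are related.

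**Step 3. Waitlist.** With an assumed 20–30% of schools on the waitlist, a gap of 4 or more waitlisted schools occurs in about 25–31% of allocations with three lists, against about 12% with twelve.

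**Step 4. Price of crossing everything.** More lists mean more incomplete blocks. The mean difference in total schools between arms is about 1.1 with three lists, 1.7 with six and 2.4 with twelve (20% on the waitlist, schools assigned to the three SES levels at random). Twelve lists of about 4.7 schools hold little more than one block each.

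**Step 5. What a gap means for the outcome.** If metropolitan and non-metropolitan schools differed by 0.2 SD on the primary outcome (assumed), an unadjusted contrast would move by 0.2 × 4/28 = 0.03 SD for a gap of 4 and by 0.2 × 6/28 = 0.04 SD for a gap of 6. The target effect is 0.25 SD.

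**Step 6. Sample size is unaffected.** The design effect is 1 + 18 × 0.05 = 1.9. At 80% power and two-sided 5% (alpha assumed), 252 per arm × 1.9 = 478.8 students, and 478.8/19 = 25.2 schools per arm. With 28 per arm, power is 84.1% (normal) or 82.8% (t, 54 df), consistent with the stated minimum of 80%.

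**The case against.** The strongest reply is that this is a descriptive slip in a condensed article. The allocation code is not shown and may have crossed all the factors. Under any of these schemes schools are randomised 1:1, so a chance imbalance is part of ordinary sampling variability, and Step 5 suggests a small shift. The higher imbalance figures also assume that location is unrelated to SES.

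Most of this stands, and it limits the conclusion. Three stronger readings might be inferred, and the documents do not support them:

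- **That two factors were in fact not implemented, and the report will claim a stratification that never took place.** The text shows an inconsistent description. It does not show which sentence governed the allocation.
- **That the comparison is confounded.** An unstratified factor under valid randomisation gives no bias in expectation. A particular allocation may be unbalanced, which costs precision and face credibility.
- **That the waitlist marks schools about to receive a competing program.** {11d} describes generalist staff development in a therapeutic framework, distinguishes it from self-regulated learning, and gives no delivery dates.

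Nor are blocks of 4 at fault in the scheme as described: at about 18.7 schools per list they work well. Sparse cells become a problem only if all three factors are crossed.

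The reply does not remove the contradiction. The article chose to state the number of lists, their index and the block size, and those details conflict with the factors it declares. That is an error in what is stated, not detail left to a fuller document.

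**Conclusion.** The concern holds as an internal contradiction about the stratification factors. {16a} declares two factors and describes lists for one; {11d} declares a third that {16a} omits. The textual mismatch is certain and needs no assumption.

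Its practical size is modest. If the three lists are used as written, a gap of 4 or more non-metropolitan schools is likely in roughly a fifth to a third of allocations, against about one in fifty with six lists. These figures assume 56 schools, equal SES strata, and non-metropolitan shares that the documents do not give. Validity of the randomisation, concealment and sample size are untouched. Severity: should-fix.

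**What to change.** **Before allocation.**

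- Make {11d} and {16a} name the same factors, and state the number of lists.
- Use one list per SES-by-location cell, six in all.
- Handle the waitlist by ordering schools by waitlist status within cells, or by constrained randomisation, rather than with twelve sparse lists in blocks of 4.
- Concealment mechanism {16b} says the sequence is generated once recruitment is complete, so cell sizes will be known. Allocate as near to half of each cell as possible; exact halves are impossible in odd-sized cells.
- Keep a record of the lists used.

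**If allocation is already done.** This is plausible, since Trial status has recruitment closing by 12 April 2024 and Participant timeline {13} starts the intervention in the term beginning 29 April. Report the factors that actually constrained the allocation, correct the text, and adjust the analysis for SES, metropolitan status and waitlist status.

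**Cost.** A few lines of Stata code and a text correction beforehand; afterwards, a reporting correction and three school-level covariates. No extra schools or data collection are needed beyond the waitlist match already planned. Six lists raise the expected difference in total schools per arm slightly, from about 1.1 to 1.7 if blocks of 4 are kept; near-half allocation within cells limits this.
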